| name | [name] |
| location | [name] |

［Evaluator］

| organization | Department of Rehabilitation Medicine, Hamamatsu University School of Medicine |
| --- | --- |
| name | [name] |
| location | [name] |

［Research equipment provider］

| organization | Saciperere Japan |
| --- | --- |
| location | [name] |

［Contract manufacturer of research equipment］

| organization | TAK SYSTEM INITIATIVE CORPORATION |
| --- | --- |
| location | [name] |

**2. Matters related to the background of the clinical trial (including matters related to the outline of the drug product)**

2-0. Outline

Clinical Question: There are many self-care devices for stiff shoulders on the market, but their efficacy and mechanism have not been sufficiently verified.

Patient: Persons over 20 years old who are aware of stiff shoulders.

Intervention: Perform optical acupuncture.

Comparison: None

Outcome: Relief of subjective symptoms of stiff shoulders and clarification of the mechanism

Research Question: Will a single treatment using an LED acupuncture device on adults with shoulder stiffness cause any change in pain threshold evaluated by tenderness meter, subjective symptoms (shoulder stiffness, pain) evaluated by VAS, autonomic nerve function evaluated by Finapres NOVA, and baroreceptor reflex sensitivity compared to before the treatment. The results will be compared with those before the treatment to see if any changes occur.

2-1. Background and Significance of Clinical trial

(a) Current status of healthcare products and positioning of this research and development

In the Health and Medical Care Strategy approved by the Cabinet on March 27, 2020, the promotion of the healthcare industry outside the public insurance is mentioned as a new industry creation that contributes to the formation of a healthy and long-lived society. (PD: [name]), and the development of healthcare devices has become one of the pillars of the national strategy in health promotion and industrial growth. Against this backdrop, Sasiperere Japan Ltd. has embarked on the development of self-care products targeting "stiff shoulders. It is known that a large number of people are aware of stiff shoulders (see below), and in addition to visiting a medical institution to treat the underlying disease, massage and acupuncture, and moxibustion are widely used to deal with this problem. Acupuncture and moxibustion are performed by acupuncturists who have specialized skills and knowledge and are nationally certified. Sasiperere Japan Ltd. has been developing an LED light acupuncture and moxibustion device to provide a painless, safe, compact, and easily usable device for general users by converting the specialized skills of acupuncturists into IOT.

Associate [name] of the Graduate University for the Creation of New Photonics Industries and Sasiperere Japan Ltd. has been selected by the Hamamatsu Photon Valley Center, Hamamatsu Regional Innovation Promotion Organization, to participate in the 6th A-SAP Industry-Academia-Government-Finance Collaborative Innovation Promotion Project for FY2020, for "obtaining evidence of the efficacy of LED optical acupuncture. A clinical trial was planned to clarify the actual clinical efficacy in humans using the LED optical acupuncture device. The purpose of this R&D project is to use a prototype LED optical acupuncture and moxibustion device for single-use on people who are aware of stiff shoulders and to examine whether or not the device improves symptoms, is safe, and affects physiological indices. In the future, using this research as a step, the company aims to develop a device that enables the identification of "acupuncture points" using AI in combination and launch it as a health care product.

(b) Status of target diseases in Japan and overseas (including epidemiological data on target diseases)

Shoulder stiffness is a subjective symptom, generally a syndrome "characterized by symptoms and complaints of discomfort, discomfort, and dull pain mainly caused by muscle tension from the lower occipital area to the posterior neck, back of the shoulder blade, and shoulder joint.^1)^ According to the 2019 National Survey of Living Conditions (Ministry of Health, Labour and Welfare, Office of Household Statistics, Ministry of Health, Labour and Welfare, July 17, 2020), 57.2/1000 males (2nd highest prevalence) and 113.8/1000 females (1st highest prevalence) were affected by the syndrome.^2)^

(Figure, Top 5 Symptoms of Prevalence by Gender, reproduced from the 2019 National Survey of Living Conditions)

Causes of stiff shoulders are classified as intrinsic (primary), symptomatic, and psychogenic. Intrinsic causes are those that have no underlying disease and are considered at risk from poor posture, muscle weakness due to lack of exercise, inappropriate exercise, overwork, cold, stress, and aging. Symptomatic stiff shoulders can be caused by a variety of underlying conditions, including cervical spine disease, diseases that cause dysfunction of the shoulder joint, and abnormalities in the musculature of the shoulder and neck region. In the psychiatric field, stiff shoulders are often reported in patients with panic disorder, psychosomatic disorders, and depression.^3)^ In addition, stiff shoulders are known to be induced by generalized anxiety and tension in the posterior neck muscles.

(b) History and details of standard treatments that have been implemented to date.

For treatment of shoulder stiffness, treatment of the underlying disease is given priority if it is symptomatic. For essential shoulder stiffness, drug therapy such as trigger point injections, nerve blocks, intervertebral disc injections, intervertebral joint blocks, and nonsteroidal anti-inflammatory analgesics, physical therapy, heat therapy, acupuncture, and phototherapy using low-frequency acupuncture and low power laser, linearly polarized infrared light, etc. are used.

On the other hand, according to the summary of the 1998 National Survey of Living Conditions, more people complaining of stiff shoulders receive treatment at anma, acupuncture, moxibustion, and other treatment centers (54.0%) than at hospitals (23.4%) or clinics (25.7%)^4)^, indicating that not only treatment at medical institutions but also osteopathic clinics and ^4)^, and in many cases, patients receive treatment not only at medical institutions but also at osteopathic clinics and massage parlors, or are treated only by self-care.

(c) Current Standard of Care and Outcomes

As a treatment involving medical treatment, Morimoto et al. reported the results of trigger point injections using a combination of dibucaine hydrochloride and corticosteroids. The report showed a 54% reduction in pain as measured by a visual analog scale.3) Bogduk et al. reported that intervertebral joint block resulted in complete pain relief in 16 of 24 patients.^5)^

5) As for the results of acupuncture and other treatments, Hayashi et al. studied the effects of low-frequency acupuncture on patients with shoulder stiffness for more than one year and reported that treatment improved subjective symptoms of shoulder stiffness and muscle hardness.^6)^ In addition, Kishi et al. ^7)^ However, the evidence for the treatment of stiff shoulders in the field of Oriental medicine is not yet sufficient.

In the field of optical acupuncture and moxibustion, which is the subject of this evaluation, laser-based optical acupuncture and moxibustion have been used for some time. There are also some self-care products available on the market (available for several thousand yen to 20,000 yen via online shopping, etc.). Laser acupuncture has the advantage of being less invasive and requiring less time than conventional acupuncture. On the other hand, the characteristics of lasers (monochromatic, directional, and high coherence) make them unsafe, and strict regulations are imposed on their use. In the past literature on optical acupuncture and moxibustion, parameters such as wavelength, irradiation amount, beam shape, skin thickness of the irradiated area, and age of the research subjects varied, making uniform interpretation difficult,^8)^ and the mechanism of efficacy of optical acupuncture and moxibustion is not well understood.^9)^

(d) Issues, uncertainties, etc. in the current standard treatment that lead to the need for such clinical trial

As mentioned above, stiff shoulders are a very popular ailment, and while treatments such as trigger point injections are effective, on the other hand, people often receive acupuncture, moxibustion, massage, and other treatments without visiting a medical institution. There are a large number of health care devices on the market for stiff shoulders, and the need for such devices is high. Although these health care devices are inexpensive and readily available, scientific verification of their effectiveness is not yet sufficient.

The optical acupuncture device used in this study can generate near-infrared light with a wavelength of 780 nm at an output of 750 mW. Several papers have reported the effects of near-infrared light on the body, including selective inhibition of peripheral nerve excitation conduction, relaxation of vascular smooth muscle, and dilation of arterioles due to sympathetic nerve inhibition.^10,11)^ In animal experiments using rabbits, Komori found that direct irradiation with linearly polarized near-infrared light caused dilation of the auricular arterioles' diameter, blood flow velocity, and blood flow rate. ^12)^ Based on these results, we expect that the same effects will be observed with this acupuncture device. We will use the LED optical acupuncture device in this research project on people who are aware of stiff shoulders and evaluate its safety and effectiveness in relieving symptoms of stiff shoulders, as well as whether it has a favorable effect on physiological tests such as skin temperature, autonomic nervous system, and electromyogram. If the safety and effectiveness of this device are proven, the possibility of evidence-based self-care for stiff shoulders will be found, and its commercialization in the future will improve the health of many people and contribute to the realization of an unaffected, healthy, and long-lived society and a reduction in social security costs.

**2-2.** **Information on medical devices used in the clinical trial**

| Classification | 78 Electrotherapy Apparatus for Home Use |
| --- | --- |
| Generic name | Household infrared therapy apparatus |
| Medical device Class | II |
| Trade name | LED light acupuncture and moxibustion device |
| Purpose or effect | Relief of symptoms of stiff shoulders |
| Usage | Irradiation to acupuncture points |

**LED light acupuncture and moxibustion device**

[figure not shown]

**irradiation device　　　　irradiation section (skin contact section)**

**
[figure not shown]

[figure not shown]
**

silicone rubber

Light Source

LEDs are not monochromatic but broadband light, less directional than lasers, and noncoherent, and are therefore considered safer than lasers. Nevertheless, the 780 nm wavelength is a concern for thermal injury to the retina, low visible light thermal injury to the retina, and infrared radiation injury, so the device is equipped with a safety mechanism that allows the LED to be irradiated only when grounded to the skin.

**3. Matters Related to the Purpose of the Clinical Study**

To verify whether a single treatment using an LED acupuncture device (wavelength 780nm±15nm, output 750mW) on adults who are aware of stiff shoulders causes changes in subjective symptoms (stiffness and pain in the shoulders) evaluated using VAS, pain threshold evaluated using a tenderness meter, autonomic nerve function evaluated using Finapres NOVA and baroreceptor reflex sensitivity, as compared to before the treatment.

**4.** **Matters related to the content of the clinical trial**

**4-1.** **Primary and secondary endpoints**

**4-1-1.** **Primary endpoints**

Subjective symptoms (VAS)

**4-1-2. Secondary endpoints**

Skin temperature, pressure pain threshold, heart rate variability, baroreceptor reflex sensitivity, adverse events

**4-1-3. Exploratory endpoints**

Muscle properties observed on ultrasonography (brightness, muscle contraction, muscle thickness, etc.), changes in surface electromyography (amplitude, frequency, etc.)

**4-2.** **Types of clinical trials, methods, and procedures**

**4-2-1.** **Number of cases**

Planned case enrollment　10 cases
Subjects will be publicly recruited by posting posters, etc.

**4-2-2.** **Trial period**

The expected period of participation of research subjects: approximately two to three days per week

Observation period (enrollment of the first case - completion of data collection for all endpoints): February 1, 2021, to June 30, 2021

Total study period: February 1, 2021, to March 31, 2021

**4-3.** **Inclusion and exclusion criteria for study subjects**

**4-3-1.** **Inclusion criteria**

The following selection criteria will be applied to those who meet all of the following criteria

1. men and women 20 years of age or older

2. who are aware of shoulder stiffness

3. Persons who have given their consent to this study by signing a consent form.

**4-3-2　Exclusion criteria**

Patients who meet at least one of the following exclusion criteria will be excluded.

1. those with diseases of the cervical spine (cervical spondylosis, herniated disc, intervertebral arthritis, cervical sprain, etc.)

2. those who are being treated by a physician for stiff shoulders

3. who habitually receive treatment for stiff shoulders or self-care (e.g., compresses, oral medication, acupuncture, moxibustion, massage)

4. who has skin abnormality from the neck to the back

5. who are deemed inappropriate by the Principal Investigator (or Co-Principal Investigator).

**4-4.** **Methods of enrollment, randomization, blinding of study subjects**

**4-4-1** **Enrollment of Study Subjects**

After obtaining written consent as a research subject, the principal (sub)investigator will ensure that all selection criteria are met and all exclusion criteria are not violated. The principal investigator (or sub-principal investigator) will then assign an identification code, complete the screening roster, and enroll the research subjects.

**4-4-2.** **Randomization Blinding Methods**

Not applicable to this study.

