**4-6 Research Procedures**

**4-6-1 Research implementation system**

This clinical trial will be conducted as part of the "Obtaining Evidence of Efficacy of LED Optical Acupuncture and Moxibustion" project (project leader: [name], Graduate University of the Creation of New Photonics Industries), which was adopted as an industry-academia-government-finance collaboration innovation promotion project, and for which Sasiperere Japan Ltd. applied. The LED acupuncture and moxibustion device to be evaluated is an unapproved medical device, and the clinical trial to be conducted to evaluate its safety and efficacy falls under the category of specified clinical trial and must therefore be conducted at a medical institution. Therefore, the University decided to participate in the project. Neither the principal investigator ([name]) nor the sub-investigator ([name]) has acupuncture and moxibustion skills or national certification, so the treatment will be performed by Zenba Acupuncture and Moxibustion Clinic's [name] (acupuncturist) under the supervision of Drs. (former professor at St. Christopher's University, now Health Data House Corporation (Iwate University venture)) and [name] of the Graduate University for the Creation of New Photonics Industries will be in charge of echo, electromyography, and thermography, while [name] of the University will be in charge of baroreceptor reflex sensitivity and autonomic nerve function.

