**4-6-2　Protocol Treatment**

　Study Design

Single-arm, open-label, uncontrolled, single-comparison study

Treatment with research equipment

Efficacy and safety assessment

Obtaining written consent

Eligibility Verification and Registration

<Protocol Treatment>

The position of the patient during the protocol is the sitting position, and the following order is used.

[At the time of obtaining consent]

After obtaining consent, a questionnaire (background investigation) will be conducted.

[Before treatment]

1. After resting for 5 minutes, vital signs will be measured.
2. The research subject will fill out the questionnaire (before the procedure).
3. Observe the skin at the treatment site.
4. Measurements will be made in the following order: muscle ultrasonography of both shoulders, surface electromyography, thermography, and pressure pain threshold. At the end of the electromyography, continuous blood pressure monitoring and continuous measurement of heart rate variability are performed.
5. The results of the examination are confirmed, and the treating side is decided.

(Criteria for determining the treating side)

The side with the lower pressure sore meter reading is the treatment side.

[Treatment] 1.

1. irradiate LED light acupuncture needles to the shoulder well (a common acupuncture point for stiff shoulders).

（Irradiate the silicon rubber part of the LED acupuncture needle directly onto the skin of the shoulder well for 30 seconds per irradiation. After irradiation, check the condition of the skin, and continue irradiation after 3 seconds until the skin shows a reddish change to the naked eye from before irradiation. Repeat irradiation up to 6 times.

[Immediately after the treatment]

1. Immediately after the LED acupuncture irradiation, skin observation, thermography, and pressure pain threshold (on the treated side only) should be performed. (After the measurement, cover the treated area with a bath towel.
2. The research subject will fill out the questionnaire (immediately after the treatment).

[15 minutes after the treatment].

1. 15 minutes after the end of irradiation, skin observation, thermography, pressure pain threshold (on the treated side only), muscle ultrasonography, and surface electromyography are measured in this order. The Finapres NOVA will be removed when the tenderness meter measurement is completed.
2. The research subject will fill out a questionnaire (15 minutes after the treatment).

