**4-11.** **Identification of source documents**

Source documents are data and other records obtained through a clinical trial. Electronic data such as case report forms, questionnaires, and acquired images are considered source documents.

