**Description maintenance (description error)9-1-4** **Exploratory analysis**

- Compare the changes (amplitude, frequency) in surface electromyography due to weight loading before and after 15 minutes of treatment
- Muscle properties (luminance, muscle contraction, muscle thickness, etc.) observed by muscle ultrasonography will be compared before and 15 minutes after the treatment.
- ~~Comparison of baroreceptor reflex sensitivity before, immediately after, and 15 minutes after the procedure~~

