**18-4.** **Attribution of Results**

The ownership of the results, data, and intellectual property rights obtained from this research will be discussed separately with Hamamatsu University School of Medicine and The Graduate School for the Creation of New Photonics Industries.

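### Blinding is set aside altogether, although stored ultrasound, EMG and thermography files could be read with the time point masked

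*Protocol*

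**What the plan says.** Section 4-6-2 of the protocol describes a "Single-arm, open-label, uncontrolled, single-comparison study". On randomization and blinding, section 4-4-2 says only "Not applicable to this study", and section 4-10 refers back to it. The parent heading, 4-4, reads "Methods of enrollment, randomization, blinding of study subjects".

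Section 4-6-1 assigns the measurements. A person "of the Graduate University for the Creation of New Photonics Industries will be in charge of echo, electromyography, and thermography"; the sentence is damaged but appears to add a second person, now at a data company. The same section gives that Graduate University as the affiliation of the leader of the project set up to obtain evidence of efficacy. Baroreflex sensitivity and autonomic function are assigned to the medical institution instead.

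On storage, section 4-11 says "Electronic data such as case report forms, questionnaires, and acquired images are considered source documents". Section 13-1 has records anonymised before they go to outside institutions, and describes this in terms of the subject's identity only. On analysis, section 9-1-4 says "Muscle properties (luminance, muscle contraction, muscle thickness, etc.) observed by muscle ultrasonography will be compared before and 15 minutes after the treatment", with a parallel comparison for surface EMG. Section 9-1-3 tests skin temperature at three time points.

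**The concern.** Every efficacy contrast in sections 9-1-2 to 9-1-4 is within subject, before against after, with no comparator. A reader who knows that a file comes from after treatment therefore knows the equivalent of the treatment allocation. Ultrasound luminance and thickness, the EMG segment taken from a loading period that may be cut short, and the skin area of roughly 10 cm around the irradiated site can all involve a choice of region or segment. If expectation influences that choice, there is no control arm in which the same influence would appear and cancel.

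This matters because the primary endpoint is an unblinded self-rating, and section 2-0 also names clarification of the mechanism as an outcome. The physiological measures are what would support that second aim. Affiliation with the project's lead institution is an ordinary reason to mask readers and implies nothing about anyone's conduct.

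**Working it through.** The plan states no figure on this point, so there is nothing to reproduce. Section 9-3 says that the sample size has no statistical basis. The check has two parts.

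**1. Which measures can be masked, and what it would protect**

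| Measure | Endpoint level (4-1) | Time points | Can the time label be masked at reading? |
|---|---|---|---|
| VAS | Primary | 3 | No, self-rated |
| Pressure pain threshold | Secondary | 3 | No, measured live |
| Skin temperature (thermography) | Secondary | 3 | Where feasible; fresh warming may show |
| Heart rate variability, baroreflex sensitivity | Secondary | 3 | Not usefully; see below |
| Ultrasound | Exploratory | 2 | Yes |
| Surface EMG | Exploratory | 2 | Yes, where segments are chosen by hand |

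Heart rate variability and baroreflex sensitivity come from one continuous record. Section 9-1-3 fixes 5-minute windows for heart rate variability before, immediately after and 15 minutes after the procedure, and compares baroreflex sensitivity at the same three points. Those stretches can be found only by reference to treatment time, and the work lies with the medical institution. They are left out of the proposal.

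**2. What a reader shift would do**

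Let δ be the true mean change and b the systematic difference between a reader's after and before readings. The mean paired difference then has expectation δ + b. Its standard error is SD/√n, so b does not shrink as n grows. With δ = 0, the paired t statistic has noncentrality (b/SD)·√n.

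Inputs: n = 10 planned (4-2-1), with about 5 to 7 as the evaluable minimum (9-3); significance level 0.05 (9-4). Assumptions: a two-sided paired t-test on one before/after contrast, and the values of b/SD, which the protocol does not give.

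Example: with b/SD = 0.5 and n = 10, the noncentrality is 0.5/(1/√10) = 1.58.

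| b/SD (assumed) | False-positive rate, n = 5 | n = 7 | n = 10 |
|---|---|---|---|
| 0 | 5.0% | 5.0% | 5.0% |
| 0.2 | 6.4% | 7.4% | 8.8% |
| 0.3 | 8.2% | 10.3% | 13.6% |
| 0.5 | 14.1% | 20.1% | 29.3% |
| 0.8 | 28.1% | 42.8% | 61.6% |

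A shift of 1.58 standard errors is not a borderline result by itself. On 9 degrees of freedom the critical value is 2.26, and t = 1.58 has a two-sided p of about 0.15. The harm is that the shift adds to chance variation and raises the error rate as tabulated.

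**The case against.** The strongest reply is that the line in 4-4-2 is the normal answer for an open-label single arm, under a heading about blinding of study subjects, and that it does not forbid masked reading. An SAP or imaging manual, not available here, could provide it. This stands to the extent that the line is too broad rather than false. It remains the protocol's only statement on blinding.

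A reader might infer that files are in fact read with the time point known. The protocol does not say so. It describes no reading procedure, and being in charge of a measurement may mean acquiring it. What can be said is that no masking is provided.

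A reader might also infer that staff of the project's lead institution handle all the stored images and signals. Section 4-6-1 does not support that: the autonomic and baroreflex signals are with the medical institution, and a second person appears to share the imaging and EMG work. Section 18-4, on ownership of results, names the medical school as well as the Graduate School, so it does not single out one party.

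There are practical limits too. A reader who also acquired the files may recognise them, probe placement and loading effort stay unmasked, and masking adds little where an output is automated. These points reduce the benefit without removing it. The shift sizes are assumed, so the error rates illustrate sensitivity and are not an estimate for this trial.

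**Conclusion.** The point holds within narrow limits. The protocol sets blinding aside in one line and provides no masked reading, although masking the time label is possible for stored ultrasound images, manually segmented EMG files and, where feasible, thermography images. Any reader expectation would enter the before/after change one for one. Its actual size is unknown, and the range in the table depends wholly on assumed shifts.

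The benefit covers the exploratory ultrasound and EMG endpoints and the secondary skin temperature endpoint. The primary VAS, pressure pain threshold, heart rate variability and baroreflex sensitivity are unaffected. The conclusion assumes that someone chooses regions or segments by hand, and that EMG recordings are kept: section 4-11 names acquired images explicitly and covers EMG only through its general reference to electronic data. This is a cheap improvement to a feasibility study, not an error that undermines it.

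**What to change.** Replace the line in section 4-4-2 with text along these lines:

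- Treatment, VAS and pressure pain threshold are open-label.
- Stored ultrasound images, manually segmented EMG files and, where feasible, thermography images receive random codes that show neither subject nor time point, at the anonymisation step already set out in section 13-1.
- Regions and segments are set, and values locked, on the coded files. The codes are opened only afterwards.
- Readers are identified by role. Where masking is not feasible, the reason is given.

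Heart rate variability and baroreflex sensitivity stay as planned.

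The cost is one recoding task. With 10 subjects, ultrasound and EMG at 2 time points each and thermography at 3, it covers at most 10 × (2 + 2 + 3) = 70 subject-by-time file sets. No new visit, procedure or assessor is needed. The protocol gives no figure for the effort, so calling it small is a judgement from that count. Masking will be imperfect where warming shows on thermography or where the reader acquired the file, and acquisition itself remains unmasked.
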